#### Secondary aims and sensitivity analyses on validity

Whereas our primary analysis will include all persons interviewed regardless of modality, in these secondary analyses, we will describe and compare validity between web and phone-based survey modalities. We will perform analyses for each cancer site and control for demographic and clinical factors, such as age, sex, race/ethnicity, health system, and web vs. phone completion of the questionnaire. If there are statistically significant differences between web and phone-based surveys with respect to agreement measures, we will consider statistical adjustments for analyses or presentation by separate modality where we have sufficient sample sizes.

We will also conduct a per-protocol analysis (including only those surveyed with the assigned modality) and an as-surveyed analysis (including all respondents according to the completed survey modality). A Wald-based test will be used to assess the statistical evidence for differences across subgroups (*p*<0.05, with no adjustment for multiple testing).

We will further use a multivariable logistic regression model of participants’ reported screening status (not answering “yes/no”, but “correct/incorrect” answer) as a function of actual screening status (i.e., whether and how recently they have been screened) to estimate the degradation of recall over time. We will perform analyses for each cancer site and control for demographic and clinical factors, such as age, sex, race/ethnicity, health system, and web vs. phone completion of the questionnaire. Heterogeneity in the relationship between actual and reported screening status will be accounted for by modeling the interactions between actual screening status and the factors listed above on the outcome of reported screening status.

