### Design

In order to test whether mode of survey administration affected cancer screening question validity, we are embedding the surveys within a randomized trial of phone- vs. web-based survey questions about breast, colorectal, cervical and lung cancer screening compared to gold-standard data from EMRs. To measure the reliability of the cancer screening questions, we simultaneously randomize participants to receive a follow-up survey either 1- or 3-months after initial survey completion.

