### Stratification and randomization

We extract data on prior cancer screening from EMRs using Common Procedural Terminology (CPT) codes, International Classification of Disease (ICD) codes, and home-grown codes from each health plan. Participants are stratified by screening status into three groups based on EMR data: up to date with screening based on USPSTF recommendations, screened in the past five years but not up to date with their screening, and eligible but not screened in the past five years. Participants are stratified by race and ethnicity with the goal of recruiting at least 25% Non-Hispanic Black participants and 25% Hispanic participants for the study population. If not enough available participants are available to recruit from a given stratum, we select additional participants from other strata. Random samples of eligible participants from each study site are sent to the UW Data Coordinating Center (UW DCC) for stratified randomization for initial survey modality (phone vs. web) and subsequent survey timing (1 vs 3 months) on a regular basis at KPWA, UW, and MHS. Due to administrative requirements at HFH, patients at this site ware randomly assigned to their survey modality but not their follow-up time. We select HFH patients for participation in two waves. Those selected in May 2023 were assigned to 3-month follow-up, whereas those selected in August 2023 were assigned to 1-month follow-up. To maximize study efficiency, we select people who are eligible for more than one screening exam based on EMR information. For example, we combine cervical and breast cancer screening questions for women ages 40–49 and breast, cervical, and colorectal cancer screening for women aged 50–65 (Table 2).

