### Recruitment and data collection

Each site is responsible for the recruitment and interviewing of participants from their healthcare system. As described above, each site regularly sends samples of eligible participants to the UW DCC for stratified selection and randomization. The UW DCC returns a list of randomized study participants back to each site. Staff from each site mails recruitment and study information letters to these potential participants. The recruitment letters include information on their assignment to either the phone or web survey. If assigned to the web survey, the recruitment letters include a survey link and QR code along with a unique study ID in two parts (ID and PIN). If assigned to the phone survey, potential participants are notified in the letter that a member of the study team would be calling them to conduct their interviews. Trained interviewers call participants one week after the letters are sent. Participants are called up to 5 times if they do not complete the survey online or are unavailable by phone. For each group, we offer the option to complete the survey via an alternate modality for participants who ask for this option (i.e., phone participants are emailed a web link if they preferred to complete it online and web participants are offered the opportunity to do the survey over the phone).

Invited participants complete eligibility questions and if eligible, respond to the cancer screening questions. The cancer screening survey questions include questions on whether the participant had received cancer screening exams, when they received their most recent cancer screening exam, the type of exam they received, and the main reason for their most recent screening exam. Participants are asked the most important reason for not being screened if the participant has not recently received a cancer screening or is not up to date with the specific type of cancer screening.

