For sensitivity, specificity, PPV, NPV, and concordance we will calculate 95% confidence intervals based upon the binomial distribution. Sensitivity and specificity indicate the effectiveness of a test (here the NHIS survey result) with respect to a trusted “outside” referent, while PPV and NPV indicate the effectiveness of a test (the NHIS survey result) for categorizing people as having or not having a target condition/screening [37].

We will also calculate the report-to-records ratio, the ratio of participants reporting a test (true positives plus false positives) divided by the percentage of tests in the record (true positives plus false negatives). The report-to-records ratio is a measure of net bias in test reporting, where values >1.0 denote overreporting and values <1.0 denote underreporting [38]. All measures will be calculated for each cancer screening test type, as well as by mode of survey administration. For reports to records ratio, 95% confidence intervals will be generated using bootstrap resampling [39].

In our analysis, we will compare our accuracy measures for those completing the survey by web vs. phone. Because survey modality (phone vs. web) was randomly allocated, and we allow participants to change their mode of completion when we contact them, we will perform both an intent-to-treat analysis as well as a separate analysis by modality used.

For responses to the question ‘when did you have your most recent test to check for [cervical/breast/colorectal/lung] cancer’, we hypothesize response accuracy will vary based on the length of time since the last screening exam. We will present the proportion of patients who answer ‘yes’ to having had screening stratified by ranges of time between the survey date and time of last screening exam, including a stratum for those who have not had this exam within the study reporting period of 5 years. In addition, we will present the proportion of patients who had screening exams, within these ranges of time, among those who answer ’yes’ or ’no’ to each question. All analyses will be stratified by cancer site.

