#### Missing data

Missing data due to non-response on both survey waves will be investigated in-depth to look for potential associations with participant demographic factors or with responses to the previous survey. We will use a multiple imputation approach as a sensitivity analysis to examine the extent to which missing data may influence the observed reliability results.

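### The adjusted phone versus web comparison lists completed mode as a control variable, and the separate intent-to-treat comparison covers respondents only, with no stated check of response by assigned arm

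*Protocol article*

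**What the plan says.** The Design section gives the purpose of the randomization, which is to learn whether survey mode affects question validity: "we are embedding the surveys within a randomized trial of phone- vs. web-based survey questions".

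Under Recruitment and data collection, randomization comes first: "The UW DCC returns a list of randomized study participants back to each site". The invitation then tells people their arm: "The recruitment letters include information on their assignment to either the phone or web survey". Eligibility questions follow, and either arm may switch mode on request.

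The mode comparison appears in two places:

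- **Primary aims and analyses on validity.** Because mode was randomized and "we allow participants to change their mode of completion when we contact them, we will perform both an intent-to-treat analysis", together with a separate analysis by the mode used. No covariates are named here.
- **Secondary aims and sensitivity analyses on validity.** The first paragraph states that "we will describe and compare validity between web and phone-based survey modalities". Its next sentence says the analyses will "control for demographic and clinical factors, such as age, sex, race/ethnicity, health system, and web vs. phone completion of the questionnaire". A significant web/phone difference is then the trigger for considering adjustment or separate presentation by mode. Per-protocol and as-surveyed analyses follow.

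The covariate sentence recurs in the recall-model paragraph of the same section.

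On non-response, the Missing data section plans to relate it to demographic factors and earlier answers, and uses multiple imputation "to examine the extent to which missing data may influence the observed reliability results". Limitations adds that response rates can be estimated by screening status. Neither place mentions assigned mode. Screening status is known for everyone randomized: "Participants are stratified by screening status into three groups based on EMR data".

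**The concern.** There are two separate problems.

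**Adjustment.** If the exposure in the secondary comparison is completed mode, the model controls for its own exposure. If it is assigned mode, the model conditions on a post-randomization variable that participants may choose and through which assignment mainly works. What remains for assigned mode is then only an effect that bypasses completion, plus any selection among switchers. This has a consequence inside the plan: a difference that has been adjusted out cannot trigger the separate presentation that the same paragraph makes depend on it.

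**Respondents only.** A person knows the assigned mode before deciding whether to answer. If web and phone attract people with different recall or screening history, comparing respondents by assigned arm mixes a mode effect with a response effect. Randomization protects the comparison of all invitees, not of those who replied.

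Mode is the one randomized factor aimed at validity, so both problems bear on the answer to that question.

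**Working it through.** **1. The plan's own figures.** The Sample size section gives precision for sensitivity and specificity pooled over modes. The Wald width is 2 × 1.96 × √(p(1−p)/n).

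- n = 500, p = 0.80: 0.070 (stated <0.1)
- n = 100, p = 0.9: 0.118 (stated <0.12)
- n = 100, p = 0.8: 0.157 (stated <0.16)

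These reproduce. They do not bear on the present point, and the article states no sample size or power for phone versus web.

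**2. Effect of adding completed mode.** The document gives no switching rates or mode effect, so the inputs are assumptions: accuracy 0.82 by phone, 0.90 by web (completed-mode effect d = 0.08), and switching rates c_web and c_phone of 10 to 30%. If assignment acts only through completion and switching is unrelated to accuracy, then

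assigned-mode difference = d × (1 − c_web − c_phone),

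and the assigned-mode coefficient given completed mode is 0.

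A simulation of 400,000 people per scenario fitted a linear probability model with assigned mode alone, then with assigned and completed mode together. The last column lets a latent factor drive both switching and accuracy.

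| Switching web / phone | Formula | Assigned mode alone | Plus completed mode, switching unrelated to accuracy | Plus completed mode, switching related to accuracy |
|---|---|---|---|---|
| 10% / 10% | 0.08 × 0.8 = 0.064 | 0.065 | 0.000 | −0.042 |
| 20% / 10% | 0.08 × 0.7 = 0.056 | 0.056 | 0.000 | −0.039 |
| 30% / 10% | 0.08 × 0.6 = 0.048 | 0.048 | 0.000 | −0.028 |
| 30% / 30% | 0.08 × 0.4 = 0.032 | 0.032 | 0.001 | −0.018 |

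With completed mode in the model, a real assigned-mode difference vanishes or changes sign.

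**3. Effect of differential response.** Assume no mode effect and two equally common types of invitee, with accuracy 0.95 and 0.75. Accuracy among respondents in an arm with response rates r₁ and r₂ is (0.95 r₁ + 0.75 r₂)/(r₁ + r₂).

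| Web response (r₁, r₂) | Phone response (r₁, r₂) | Web | Phone | Spurious difference |
|---|---|---|---|---|
| 40%, 20% | 40%, 40% | 0.883 | 0.850 | 0.033 |
| 35%, 15% | 40%, 40% | 0.890 | 0.850 | 0.040 |
| 30%, 20% | 40%, 35% | 0.870 | 0.857 | 0.013 |
| 30%, 30% | 40%, 40% | 0.850 | 0.850 | 0 |

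A lower response rate in one arm does no harm by itself. Bias arises when mode changes who responds. The article gives no response rates, so the size cannot be fixed.

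**The case against.** The strongest reply is that the plan already contains the right analysis. The primary section commits to an intent-to-treat comparison, gives switching as the reason, and attaches no completed-mode covariate. A reader might infer that the whole randomized comparison is adjusted away. The text does not support that: the circular covariate belongs to the adjusted comparison in the secondary section, and no model holding both assigned and completed mode is spelled out. This part of the reply stands.

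The covariate sentence may also have been carried over from the recall model, where mode is a proper covariate, or the mode term may simply be the modality effect in a multivariable model. The list is given as examples, so it is not a closed set. For that reason the absence of EMR screening group from it is not an error in itself. Sensitivity and specificity already condition on EMR status, and the recall model includes how recently people were screened. But completed mode is named explicitly, and a likely carry-over still needs correcting.

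On response, web invitees who do not complete online are also called, up to five times, and either arm may switch. Non-response at both waves is to be examined. These features may narrow differential response, but none of the stated checks is by assigned arm.

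A reader might also infer a large response bias. For example, suppose specificity is 0.50 in lapsed and 0.95 in unscreened people, and lapsed people make up 50% versus 20% of EMR-negative respondents. That gives 0.5 × 0.50 + 0.5 × 0.95 = 0.725 against 0.2 × 0.50 + 0.8 × 0.95 = 0.86, a gap of 13.5 points. Such an imbalance between randomized arms is extreme and has no source in the document. The example also fails for the outcome of any exam in the last five years, because lapsed people were screened within five years and are EMR-positive there.

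**Conclusion.** The point holds in two limited parts.

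1. The adjusted web versus phone comparison in the secondary section is wrong as written. Taken literally, it would move an assigned-mode difference of 3.2 to 6.5 points to about zero, or to between −1.8 and −4.2 points. These figures assume an 8-point effect of completed mode, 10 to 30% switching per arm and, for the negative values, switching related to accuracy. The intent-to-treat analysis in the primary section is not shown to share the fault.
2. That intent-to-treat analysis covers respondents only, after an assignment disclosed before response. The article states no response comparison by arm and no missing-data method for validity by arm. This is a risk of unknown size, not an established bias. The assumed scenarios give 0 to 4 points.

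The change is worth making before analysis.

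**What to change.** - **Assigned-mode comparison:** remove completed mode from the covariates. Fit assigned mode plus the randomization strata: site, three-level EMR screening group, and race/ethnicity.
- **Completed mode:** keep it as the exposure in the as-surveyed analysis and as a covariate in the recall model.
- **Intent-to-treat set:** state that it consists of respondents analysed by assigned arm. Report response by assigned mode and EMR screening group for all randomized invitees.
- **Sensitivity analysis:** weight respondents to all invitees within each arm, using a parsimonious response model such as main effects of site, EMR group, race/ethnicity and age. Fully crossed cells would be too sparse. With 4 sites, 3 EMR groups and an assumed 3 race/ethnicity and 3 age groups there are 4 × 3 × 3 × 3 = 108 cells per arm. Equal arms would have about 1,576/2 = 788 respondents each, or about 7 per cell, before splitting by cancer site.

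The cost is a change of wording, one response table and one extra analysis. EMR screening group, site and race/ethnicity already serve selection and randomization, so no new data collection is needed. The weighted analysis will have somewhat larger variance, which is acceptable for a sensitivity analysis.

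### The adjusted secondary phone-versus-web comparison lists the mode of completion, which is fixed after randomization, among its own control variables

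*Protocol article*

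**What the plan says.** All references are to the protocol article.

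- **Stratification and randomization:** sites send samples for "stratified randomization for initial survey modality (phone vs. web) and subsequent survey timing (1 vs 3 months"). Mode is therefore a randomized factor, and the Design section gives its purpose: to learn whether mode of administration affects question validity.
- **Recruitment and data collection:** the other mode is available to participants who ask for it, and those who do not complete online are called up to five times.
- **Primary aims and analyses on validity:** "Because survey modality (phone vs. web) was randomly allocated, and we allow participants to change their mode of completion when we contact them", the plan continues, "we will perform both an intent-to-treat analysis as well as a separate analysis by modality used". No covariates are attached to this statement.
- **Secondary aims and sensitivity analyses on validity, first paragraph:** "in these secondary analyses, we will describe and compare validity between web and phone-based survey modalities". The next sentence says the analyses will be done for each cancer site and will "control for demographic and clinical factors, such as age, sex, race/ethnicity, health system, and web vs. phone completion of the questionnaire". The paragraph closes by saying that, if web and phone differ significantly on agreement measures, statistical adjustment or presentation by modality will be considered.
- **Same section, second paragraph:** "We will also conduct a per-protocol analysis (including only those surveyed with the assigned modality) and an as-surveyed analysis". "A Wald-based test will be used to assess the statistical evidence for differences across subgroups", at p<0.05 without multiplicity adjustment.
- **Same section, third paragraph:** the covariate sentence recurs word for word for the logistic model of recall degradation.

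**The concern.** The variable being compared, or its direct consequence, appears among the variables held constant. Completion mode is not a baseline characteristic. It results from the random assignment plus each participant's later choice, and it is the route by which assignment can affect the accuracy of answers.

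Holding it fixed in an as-assigned comparison asks whether assignment matters among people who answered in the same mode. That is not the question the randomization was set up to answer. What remains is the contrast between switchers and non-switchers within a completed mode, and switchers are self-selected.

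At stake is the adjusted estimate of the mode effect and the decision placed beside it in the same paragraph. A spurious null would favour pooling results that in fact differ by mode. A selection artefact could prompt adjustment or separate presentation for the wrong reason.

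**Working it through.** **1. Is there a figure in the plan to reproduce?** No. The article states no mode effect, no power for phone versus web, and no switching rate. Its precision figures in the Sample size section do not bear on this point.

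**2. What completion mode is in each mode analysis the article names**

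| Analysis | Exposure | Role of completion mode | Result of adjusting for it |
|---|---|---|---|
| As-assigned | Assigned mode | Mediator, set after randomization | Effect removed, or switcher selection left |
| Per-protocol | Assigned = completed | Identical to the exposure | Not separable |
| As-surveyed | Completed mode | The exposure itself | Not separable |

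For the last two rows, a design matrix with an intercept, the exposure and an identical covariate has 3 columns but rank 2.

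The first paragraph does not say which analysis it means. Per-protocol and as-surveyed analyses are introduced afterwards as additional, so the as-assigned reading is the most natural.

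**3. Illustration A (assumed inputs).** n=500, 1:1, concordance 0.90 by completed phone and 0.80 by completed web. A share a of web-assigned people complete by phone and b=5% switch the other way. Linear probability model, 1,000 simulated trials.

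If the effect runs only through completed mode, the expected as-assigned difference is −10 × (1 − a − b) points, and the expected difference within a completed mode is 0.

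| a | Formula | Simulated, unadjusted (power) | Simulated, adjusted for completion mode (share significant) |
|---|---|---|---|
| 10% | −10 × 0.85 = −8.5 | −8.6 (0.78) | −0.2 (0.05) |
| 20% | −10 × 0.75 = −7.5 | −7.4 (0.67) | 0.0 (0.05) |
| 30% | −10 × 0.65 = −6.5 | −6.6 (0.57) | −0.1 (0.04) |

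**4. Illustration A with selective switching.** Take a=30%, with web-to-phone switchers 5 points less accurate (0.85 by phone).

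- Web-assigned: 0.70 × 0.80 + 0.30 × 0.85 = 0.815.
- Phone-assigned: 0.95 × 0.90 + 0.05 × 0.80 = 0.895.
- As-assigned difference: −0.080 (simulated −0.080, power 0.73).

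Adjusting for completion mode averages the within-mode differences with weights n₁n₀/(n₁+n₀):

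- Completed phone: difference −0.05, weight 75 × 237.5/312.5 = 57.0.
- Completed web: difference 0, weight 175 × 12.5/187.5 = 11.7.
- Weighted: −0.05 × 57.0/68.7 = −0.041 (simulated −0.041, power 0.15).

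The remaining 4 points are switcher selection, not a mode effect.

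**5. Illustration B (assumed inputs).** Logistic model, N=1,576, 80% correct by phone and 88% by web, switching equally likely in both directions, 400 simulated trials per row.

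| Switching | Assigned-mode log-OR, unadjusted (share p<0.05) | Adjusted log-OR (share p<0.05) | SE unadjusted → adjusted |
|---|---|---|---|
| 5% | 0.54 (0.98) | −0.03 (0.05) | 0.14 → 0.32 |
| 10% | 0.48 (0.94) | −0.01 (0.03) | 0.14 → 0.23 |
| 20% | 0.35 (0.73) | 0.00 (0.03) | 0.14 → 0.17 |
| 30% | 0.24 (0.41) | 0.00 (0.05) | 0.14 → 0.15 |

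The SE inflation follows from the correlation r = 1 − 2 × switching rate. At 5%, r=0.9 and 1/√(1 − 0.81) = 2.29, so 0.141 × 2.29 = 0.32.

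If switching also depends on an unmeasured trait related to accuracy (assumed), the adjusted coefficient takes the wrong sign, −0.31 to −0.13, and is significant in 15% to 28% of runs.

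**The case against.** The strongest reply is that the randomized comparison is already protected. The primary section promises an intent-to-treat analysis and attaches no covariate list to it. That stands. A reader might infer that the trial's mode question as a whole will be answered by a coefficient near zero; the article does not support this, because an as-assigned contrast free of this adjustment remains planned.

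A second reply is that the article never writes down a regression containing both assigned and completed mode. The sentence may mean only that mode is one term in the model and that its coefficient is the comparison. The closing remark about significant differences between modes fits that reading. It is possible, but it does not rescue the wording: the coefficient would then estimate the effect of a partly self-selected mode rather than the randomized one, and the text would still call the factor of interest a control variable.

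Third, the word-for-word recurrence in the recall-model paragraph suggests a copying slip. That is plausible, and a slip still needs correcting. A reader might extend the criticism to the recall model as well; that fails. The recall model estimates how correctness declines with time since screening, and the mode in which a person actually answered is a legitimate covariate there.

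Finally, the simulated sizes rest on assumed inputs. In the headline scenarios the effect runs only through completed mode, so zero after adjustment is built in. This is correct: the figures show the mechanism, not the size of the bias in this trial.

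**Conclusion.** The point holds for the adjusted secondary comparison of web and phone in the first paragraph of the secondary validity section. As written, completion mode is among its control variables, and under each mode analysis the article names it is either the mediator of the randomized factor or the exposure itself. The adjusted estimate would then be near zero, contaminated by switcher selection, or not estimable.

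The direction of the problem follows from the structure: if mode acts only through completion, conditioning on completion leaves no assignment effect whatever the true gap. Its size depends on the switching rate and the mode effect, neither of which the article gives. Under the assumptions shown, differences of 6.6 to 8.6 points become about zero, and selective switching leaves about 4 of 8 points as artefact.

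The point does not reach the intent-to-treat comparison in the primary section or the recall-degradation model. It matters because the affected comparison shares a paragraph with the decision on adjusting for modality or presenting results by it.

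**What to change.** In the first paragraph of the secondary validity section:

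- Delete completion mode from the covariate list.
- Name assigned mode as the factor of interest, adjusted only for baseline factors: age, sex, race/ethnicity and health system.
- Use completed mode as the exposure only in the separately labelled as-surveyed analysis.
- State that the decision on adjusting for modality or presenting results by it rests on the as-assigned comparison.

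Leave completion mode in the recall-degradation model. Reporting the observed switching rate in each direction would let readers judge how far the as-assigned and as-surveyed results can differ.

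The cost is a wording change in the analysis plan. Recruitment, data collection and participants are not affected.

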**Breast Cancer Screening**								
Mammography	Katz (2022) [22]				.91 (.90-.93)	.96 (.95-.97)/.78 (.73-.82)	.93 (.91-.94)/.87 (.83-.9)	
Mammography	Nandy (2016) [24]		Korean American women eligible for mammography	Accuracy of self-report of most recent mammogram date compared to medical records.	.80			
Mammography	Lofters (2015) [25]					.96(.963-.97)/.64(.63-.66)	.821(.81-.828)/.92(.91-.93)	1.18(1.16–1.20)
Mammography	Anderson (2019)		Meta analysis	Accuracy of self-report compared to medical records.	.82(.79-.86)	.96(.95-.98)/.61(.53-.69)	.80(.79-.81)/.86(.85-.87)	
Mammography	Gordon (1993) [20]				83.7	98/50.6	2.0/42.0	

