### Sample size

A minimum of 500 gold-standard positive and negative participants for each cancer type are selected to obtain confidence interval width of <0.1 for sensitivities and specificities >0.80 across all survey modalities. A total study sample size of at least 1,576 individuals will contribute information to validity analyses of cancer screening history (Fig 1). For subgroups representing 20% (n = 100) of each cancer screening cohort, highly concordant screening tests (>0.9) and tests with good concordance (>0.8) will have 95% confidence interval widths of <0.12 and <0.16 respectively. We estimate that 1,260 (80%) participants would need to be included for the assessment of test-retest reliability across all screening modalities, resulting in >0.80 power to rule out Kappa coefficients smaller than 0.61 if the true test-retest agreement is greater than 70%.

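### The Wald test planned for subgroup differences is unreliable for sensitivities near 0.95 in 20% subgroups; a score test would be better calibrated

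*Protocol article*

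**What the plan says.** Under Secondary aims and sensitivity analyses on validity, the article commits to one family of tests: "A Wald-based test will be used to assess the statistical evidence for differences across subgroups". The threshold is p<0.05, "with no adjustment for multiple testing". It gives no scale (difference of proportions or log-odds), no variance form and no rule for sparse cells.

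Under Sample size, the cohort is described as "A minimum of 500 gold-standard positive and negative participants for each cancer type are selected", aiming at a "confidence interval width of <0.1 for sensitivities and specificities >0.80 across all survey modalities". Subgroups are introduced with "For subgroups representing 20% (n = 100) of each cancer screening cohort", for which concordances of 0.9 and 0.8 "will have 95% confidence interval widths of <0.12 and <0.16 respectively". No power is stated for a difference between subgroups.

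Table 1 gives the accuracy to expect. Mammography sensitivities are 0.96 to 0.98. Pap (or Pap/HPV) sensitivities are 0.90 to 0.97, with 0.96 in the meta-analysis. Colonoscopy sensitivities are 0.91, 0.95 and 0.96. Other entries are much lower: one FOBT sensitivity is 0.32, and the meta-analytic specificities are 0.61 for mammography and 0.48 for Pap.

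**The concern.** A Wald test takes its standard error from the observed proportions. When a proportion is close to 1 and the group is small, that standard error is itself poorly estimated. At a sensitivity of 0.95 a subgroup of 50 positives is expected to produce 50 × 0.05 = 2.5 false negatives, and at 0.96 only 2. If the subgroup happens to have none, its contribution to a difference-scale variance is zero, so the statistic is inflated. On the log-odds scale the estimate does not exist.

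These tests decide which population subgroups are reported as recalling screening more or less accurately, and overreporting in particular populations is a stated motive for the study. If the real error rate is two or more times the nominal 5%, or if the test cannot see that a small subgroup is more accurate, some of those statements will be wrong for reasons unrelated to the data.

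**Working it through.** **1. The plan's own precision figures.** Normal-approximation width = 2 × 1.96 × √(p(1−p)/n).

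- n = 250, p = 0.80: 0.099. n = 500, p = 0.80: 0.070. The stated limit of 0.1 matches 250.
- n = 100: 0.118 at p = 0.9 and 0.157 at p = 0.8. Both match the stated 0.12 and 0.16.

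Since 20% of 500 is 100, the figures fit 500 participants in total per cancer type, about 250 positive and 250 negative. A 20% subgroup then has about 50 positives and the remainder about 200. The article does not state this split; it is inferred. If 500 means 500 positives, the comparison is 100 vs 400, so both are shown.

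**2. The tests**, with observed proportions p₁ and p₂, group sizes n₁ and n₂, and pooled proportion p:

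- Difference-scale Wald: (p₁ − p₂) / √(p₁(1−p₁)/n₁ + p₂(1−p₂)/n₂)
- Log-odds Wald: log odds ratio / √(sum of reciprocals of the four cells)
- Score: (p₁ − p₂) / √(p(1−p)(1/n₁ + 1/n₂))

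**3. One data set.** Subgroup 50/50 correct, remainder 190/200.

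- Difference-scale Wald: 0.05 / √(0 + 0.95 × 0.05/200) = 0.05/0.0154 = 3.24, rejected.
- Score: p = 240/250 = 0.96, so 0.05 / √(0.96 × 0.04 × (1/50 + 1/200)) = 0.05/0.0310 = 1.61, not rejected.
- Log-odds Wald: zero cell, not computable.

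At a true sensitivity of 0.95 a subgroup of 50 has no errors with probability 0.95⁵⁰ = 7.7%; at 0.96, 13.0%.

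**4. Type I error**, two-sided nominal 5%, by exact enumeration of two independent binomials (non-computable log-odds tables count as no rejection):

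| Groups | True sensitivity | Difference Wald | Log-odds Wald | Score |
|---|---|---|---|---|
| 50 vs 200 | 0.80 | 6.2% | 4.5% | 5.0% |
| 50 vs 200 | 0.95 | 9.9% | 3.0% | 3.9% |
| 50 vs 200 | 0.96 | 13.5% | 3.1% | 3.5% |
| 100 vs 400 | 0.95 | 7.1% | 3.2% | 4.9% |
| 100 vs 400 | 0.96 | 7.8% | 3.1% | 5.0% |
| 50 vs 50 | 0.95 | 5.4% | 0.2% | 4.3% |
| 125 vs 125 | 0.95 | 4.9% | 3.3% | 4.7% |

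The last row is web vs phone if allocation is 1:1.

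**5. Power at 50 vs 200:**

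| Subgroup vs remainder | Difference Wald | Log-odds Wald | Score |
|---|---|---|---|
| 0.85 vs 0.95 (subgroup worse) | 46% | 63% | 66% |
| 0.80 vs 0.95 (subgroup worse) | 77% | 87% | 89% |
| 0.95 vs 0.85 (subgroup better) | 69% | 30% | 48% |
| 0.98 vs 0.88 (subgroup better) | 87% | 12% | 65% |

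Adding 0.5 to each cell raises the 12% only to 17%. The higher difference-scale figures in the last two rows come with a test that does not hold its 5% level.

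**The case against.** The strongest reply is that the article leaves the scale and variance form open, that a full analysis plan commonly settles them, and that the two faults belong to different versions of the test. This is right as far as it goes: at 50 vs 200 no single version both over-rejects and lacks power. But the article has already fixed the word Wald, and in this setting each scale has a weakness that the score test avoids or reduces. Choosing the scale later would decide which weakness applies.

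Several limits stand:

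- A reader might infer that Wald tests are badly miscalibrated or nearly powerless throughout this analysis. They are not. The log-odds version is only mildly conservative at 50 vs 200 and nearly matches the score test when the subgroup recalls worse. The difference-scale version is close to nominal when groups are equal.
- A reader might infer that the randomised web-versus-phone comparison is compromised. At about 125 positives per mode and a sensitivity of 0.95, neither scale is inflated.
- The subgroup planning in the article concerns concordance at 0.8 to 0.9, not sensitivity at 0.95. At 100 vs 400 and 0.90 the error rates are 6.2% and 4.3%. Specificities such as 0.61 are likewise little affected (5.8% and 4.8% at 50 vs 200).
- Some of the low power is sample size. At 50 vs 50 the score test has only 39% power for 0.85 vs 0.95.
- These are secondary tests, openly unadjusted for multiplicity. The primary estimates and their intervals are untouched.

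**Conclusion.** The point holds for a defined setting: sensitivities of about 0.95 or higher, in subgroups of about 20% compared with the rest. There an unpooled difference-scale Wald test runs at roughly 10 to 13% instead of 5% (7 to 8% under the larger reading of the cohort size), against 3.5 to 5.0% for the score test. A log-odds Wald test keeps its level but is undefined in about 8 to 13% of samples. It also gives up 18 to 53 percentage points of power in the two cases shown where the smaller subgroup is the more accurate one.

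The figures assume an even split of positives and negatives, independent groups and no covariates. The article does not support a wider claim about survey mode, or about measures well below 0.95. This is a modest, inexpensive improvement to a secondary analysis, not a fault in the study's main results.

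**What to change.** In Secondary aims and sensitivity analyses on validity, replace the Wald-based test with the score test for unadjusted subgroup comparisons of sensitivity, specificity and the other proportions. For adjusted logistic comparisons, specify a score test or a Firth penalised-likelihood test where error counts are sparse. The likelihood-ratio test is not a clean substitute: at 0.95 its type I error is 7.5% at 50 vs 200 and 8.8% at 50 vs 50. Fisher's exact test is conservative (3.1% and 0.7%).

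No data, sample size or procedure changes. The cost is slightly more analysis work. Compared with a difference-scale Wald test there will be fewer nominally significant results where there is no true difference or where the subgroup is more accurate, and somewhat more power where it is less accurate. The score test does not cure the limited power of small subgroups, so estimates and intervals should remain the main output.
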